**Methods and design:**

This is a multicenter, single blind, randomized controlled clinical trial. The protocol has been approved by La Paz University Hospital Research Ethics Committee and by the Spanish Drug Agency. Two hundred and forty patients with VTE in which oral anticoagulant therapy is indicated will be included. Randomization (case/control 1:1) will be stratified by center. Acenocoumarol dose in the control group will be scheduled and adjusted following common clinical practice; in the experimental arm dosing will be following an individualized algorithm developed and validated by our group. Patients will be followed for three months. The main endpoints are: 1) Percentage of patients with INR within the therapeutic range on day seven after initiation of oral anticoagulant therapy; 2) Time from the start of oral anticoagulant treatment to achievement of a stable INR within the therapeutic range; 3) Number of INR determinations within the therapeutic range in the first six weeks of treatment.

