### Assessment variables

#### Effectiveness variables

##### Primary

• Percentage of patients with an INR within the therapeutic range (INR between 2 and 3) on day seven after the initiation of treatment with acenocoumarol.

• Time from the start of the oral anticoagulant therapy to get a stable INR within the therapeutic range (INR within the therapeutic range for three consecutive measurements for at least two weeks, with a maximum difference between the daily average doses of 10%).

• Number of INRs within the range in the first six weeks of treatment.

• Number of INRs within the range during the three months of the study.

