### Study procedures

The various study visits will be distributed as shown in Table
1:

**Table 1 T1:** Study timeline

**Day**	**−3 or −2**	**0**	**3**	**7 (±1)**	**15 (±3)**	**30 (±5)**	**60 (±7)**	**90 (±7)**
Recruitment	**√**							
Informed consent	**√**							
Selection criteria	**√**							
Medical history	**√**							
Physical examination	**√**							**√**
Blood samples for pharmacogenetics	**√**							
Randomization	**√**							
Acenocoumarol dosing (initiation/adjustment)^a^		**√**	**√**	**√**	**√**	**√**	**√**	**√**
INR determination		**√**	**√**	**√**	**√**	**√**	**√**	**√**
Evaluation of side effects		**√**	**√**	**√**	**√**	**√**	**√**	**√**

^a^In order to perform appropriate dose adjustments, additional visits can be scheduled as needed, at the discretion of the clinical researcher.

Preselection phase: The patients with VTE will be identified in the emergency department or hospital ward within the first 48 hours of the VTE diagnosis (PTE and/or DVT) and will be checked to ensure they meet the selection criteria.

Before any specific study procedure is performed, the patient will receive the information verbally and in writing through the patient information sheet. The patient must consent to participation in the study in writing (two copies). The patient will keep a copy of the information sheet and the informed consent once they have been signed. Once patients have been included in the study, the medical monitor will be informed of their inclusion and the randomization envelope will be opened to determine the study group to which they will belong.

Patients who were considered for inclusion but were not admitted to the study will be registered in a patient-log along with the cause for their non-inclusion (lack of informed consent, selection criteria, practical issues, and so on).

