Days 3 and 7 ± 1: The INR will be determined (capillary blood sample analyzed with a portable coagulometer) in both groups, and the acenocoumarol dosage will be adjusted if necessary. Control group patients will follow the dosage indications according to the standard clinical practice and visits will be scheduled for day 3, day 7 ± 1 and day 15 ± 3, depending on the length of the hospital stay. Patients included in the intervention group will have their acenocoumarol regimen readjusted according to the developed algorithm and will be scheduled for visits on day 3, 7 ± 1 and 15 ± 3, depending on the length of the hospital stay.

INR measurements will be performed on both groups and additional visits deemed appropriate for good control of the anticoagulation will be arranged. Any changes made to the dosage and all INR measurements will be recorded in the CRF and the medical records.

Visit days 15 ± 3, 30 ± 5, 60 ± 7 and 90 ± 7: During each visit, and after determining the INR (capillary blood sample analyzed with a portable coagulometer), the dosage will be adjusted. The patient's next scheduled visit will be arranged, and an additional visit will be scheduled if necessary. Adverse events will be recorded during all visits, as contained in “Adverse events” section of this protocol. During the final visit, a complete physical examination will also be performed.

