### Safety procedures and monitoring of adverse events

#### Anticoagulation monitoring

The INR (International Normalized Ratio) will be determined using a portable coagulometer (CoaguCheck®, Roche FarmaSA, Madrid, SPAIN)) during the visits on days 0, 3, 7, 15, 30, 60 and 90, to verify that the patients are properly anticoagulated and to make the necessary dose adjustments. Dosing adjustments will be performed according to standard clinical practice. For the experimental group, the genetic results will also be taken into account.

If clinically necessary, additional INR measurements and visits will be performed according to standard clinical practice.

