[33-35]. Furthermore, the risk of bleeding is also greater at the beginning of treatment; 62.5% of hemorrhages occur during the first 15 days of treatment and 79.2% occur during the first month (median, 11 days). In addition, approximately 50% of patients in therapy with anti-vitamin K have an INR >3
[36].

In addition, the improved variables that reflect appropriate anticoagulant control (time within the appropriate INR, the number of INRs in the range, and so on) could decrease the visits required for necessary monitoring and therefore improve the patient's quality of life and the cost of the entire process. Finally, the time required with VTE to properly adjust the oral anticoagulant dose (with a frequency greater than one month) is a substantial part of the total recommended treatment (three to six months). However, these two aspects are less relevant in the case of atrial fibrillation and valve replacement, in which the short-term risk of ineffectiveness is much lower and anticoagulation is required for life.

We selected appropriate anticoagulant control as the primary objective, including variables such as the percentage of patients within the therapeutic range in the short, medium and long-term or the time required to achieve control. This represents a limitation compared with the use of hard clinical variables (hemorrhages, recurrence of VTE, the progression of PTE and/or the presence of post-phlebitic syndrome). The decision to establish this primary objective was based on logistical reasons and due to its validity as a subrogated endpoint. One of the logistical reasons was the need to perform the genotypic determinations in a centralized laboratory and within a short period of time (at most two days). Therefore, the recruitment centers had to be concentrated in the city of Madrid or its suburbs. This in turn places limitations on the number of patients who could be recruited given that the study population is limited to that of the centers. Similarly, for financial reasons, the recruitment of several thousand patients was out of our reach. There is compelling evidence that maintaining an INR within the therapeutic range is a valid objective of anticoagulant therapy and is linked with clinical end-points of interest, and as such it is used routinely as a control treatment

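### Two of the four primary variables are raw counts of in-range INRs with no denominator, so a difference between arms in how often INR is measured could create or hide an effect

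*Protocol article*

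**What the plan says.** Under Assessment variables, Effectiveness variables, Primary, the third and fourth variables are "Number of INRs within the range in the first six weeks of treatment" and "Number of INRs within the range during the three months of the study". The abstract words the six-week variable in the same way: "Number of INR determinations within the therapeutic range in the first six weeks of treatment".

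Scheduled INRs are common to both arms, taken "during the visits on days 0, 3, 7, 15, 30, 60 and 90" (Anticoagulation monitoring). Beyond these, the footnote to Table 1 says that "additional visits can be scheduled as needed, at the discretion of the clinical researcher", and Anticoagulation monitoring allows further INRs when clinically needed. No maximum is set. Study procedures adds that "all INR measurements will be recorded in the CRF and the medical records". The Masking section accepts that physicians are not blinded and that this may affect the evaluation variables.

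The secondary variables include the number of special (unscheduled) INRs and the proportion of time in therapeutic range. The Discussion hopes that better control "could decrease the visits required for necessary monitoring". Statistical analysis, rule 3 for patients lost to follow-up, scores the INR of a lost visit as out of range.

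**The concern.** A count without a denominator rises when a patient is measured more often, even if control is no better. A patient with only the scheduled INRs can score at most 5 in six weeks (days 0, 3, 7, 15 and 30) and at most 7 in three months. A patient with extra INRs can exceed those ceilings.

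The number of extra INRs is decided by an unmasked physician. It is also an outcome in its own right, which the trial hopes may fall with better control. So a gain on one variable could count against the algorithm arm on two primary ones. Rule 3 does not resolve this. It gives a lost visit a defined value, but it sets no denominator and is silent on extra INRs, so an unscheduled in-range INR can offset a missed visit. At stake is whether half of the primary variables measure INR control or measure control combined with sampling frequency.

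**Working it through.** **Inputs from the article.** Scheduled INRs: 5 in six weeks, 7 in three months. In-range rates: 40% control and 60% experimental, stated for day 7 only. Alpha 0.05, beta 0.2. Recruitment target: 120 per group.

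**Inputs not in the article (assumptions).** The number of extra INRs in each arm, the in-range rate per INR at other times, and the within-patient correlation.

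**The plan's own figures.** Neither count has a sample size. The two that are given reproduce with two-sided tests:
- Day-7 status: n = [1.96·√(2·0.5·0.5) + 0.8416·√(0.4·0.6 + 0.6·0.4)]² / 0.20² = (1.386 + 0.583)² / 0.04 ≈ 96.9, so 97 per group.
- Time to stable INR: n = 2·(1.96 + 0.8416)²·21² / 10² ≈ 69.2, so 70 per group.

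**Break-even for the count.** Expected count per patient = (scheduled + extra INRs) × p, where p is the average in-range rate. With no extras in the experimental arm, the arms tie when (s + e)·p_ctrl = s·p_exp, that is, e = s·(p_exp/p_ctrl − 1).

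| Assumed in-range rates | Ratio | Extra control INRs, six weeks (s = 5) | Three months (s = 7) |
|---|---|---|---|
| 50% vs 60% | 1.2 | 1.0 | 1.4 |
| 40% vs 60% | 1.5 | 2.5 | 3.5 |

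Check of the first row: 6 × 0.5 = 5 × 0.6 = 3.0. This step needs no distributional assumption.

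**Illustrative simulation.** Six-week count, 120 per arm, binomial counts, Poisson extra INRs, z-test on mean counts. INRs are independent and the experimental arm has no extras unless stated.
- No true effect, one extra control INR on average: the count is significant in about 74%, 89% and 97% of trials at 40%, 50% and 60% in range. The proportion of INRs in range stays near 5%.
- True 50% vs 60%: about 94% power with equal measurement and about 3% with one extra control INR. With two extra, about 84% of trials significantly favour control.
- True 40% vs 60% with one extra control INR: power is still about 97%.

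**How far this depends on the assumptions.**
- No true effect, same gap of one INR, but with two extras in the less-measured arm and within-patient correlation 0.2: false positives fall to about 30%, 41% and 55%.
- Same re-test policy in both arms, each out-of-range scheduled INR repeated at most once: at 50% vs 60% the arms differ by only 0.1 to 0.5 extra INRs, the count keeps about 92–97% power, and with no true effect it is significant in about 5% of trials.

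**The case against.** The strongest reply is that the damage needs a gap of about one INR per patient that nothing in the article establishes. Re-measuring poorly controlled patients does not by itself produce it: with the same limited re-test policy in both arms, the count performs about as well as a count of scheduled INRs alone. This stands, and it limits the size of the problem. It does not remove it, because ordering is discretionary, uncapped and unmasked, so arm-dependent sampling is possible and the definition gives no protection.

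A reader might infer that the trial expects fewer INRs in the algorithm arm. The Discussion says only that better control "could decrease the visits required for necessary monitoring", as a possibility and without a size.

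A reader might also see a contradiction in the Discussion's phrase "the percentage of patients within the therapeutic range in the short, medium and long-term". That phrase is one of several examples, and the same section also refers to numbers of INRs in range, which matches the variable list.

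Finally, the sample size rests on day-7 status, with a second calculation for time to stability. Time in range and special INRs are secondary variables, so unequal sampling would be visible, and proportions could be derived from the recorded data. A full protocol or analysis plan may state which INRs count. These points lower the severity. They do not correct the primary definition as published, and choosing a denominator after unmasked data have accrued would be a post hoc change to a primary variable.

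**Conclusion.** The point holds in a limited form. As written, two of four primary variables combine INR control with measurement frequency, and no other section of the article supplies a denominator or restricts the count to scheduled visits. If measurement frequency differs by arm, the count could mislead in either direction. A true benefit cancels at 1 extra control INR in six weeks for 50% versus 60% in range, or 2.5 extra for 40% versus 60%. These break-even values rest only on average in-range rates and no extras in the experimental arm.

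The stronger reading, that the counts would hide a real benefit, is not supported. The article gives no expected number of extra INRs, and the simulated error rates need an arm-dependent gap of about one INR per patient. They shrink with within-patient correlation and are small under a common, limited re-test policy. If only scheduled INRs were intended, the problem disappears, but the article does not say so. This should be fixed; it is not a fatal flaw.

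**What to change.** Define both variables as the number (equivalently the proportion) of scheduled-visit INRs in range, with one INR per scheduled visit: days 0, 3, 7, 15 and 30 for six weeks, and those plus days 60 and 90 for three months. If a visit yields more than one reading, use the first. Score a missed visit as out of range under the existing rule 3, which then acts over a fixed denominator of 5 or 7. Keep extra INRs for the special-INR variable and for time in therapeutic range.

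The cost is a wording change to two definitions, with no new data. It should be made before any comparison by arm; the Trial status section reports 85 of the planned 240 patients included. The downside is that extra INRs no longer contribute to these two variables.

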##### Secondary

• Proportion of time within the therapeutic range, using a linear interpolation method
[27].

• Number of special INR measurements (those that are performed in addition to the scheduled measurements in the program of visits established in this protocol: days 0, 3, 7, 15, 30, 60 and 90).

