## Methods

### Design and setting

The clinical trial was designed as a pragmatic, randomized, parallel two-arm, single blind trial to compare the individualized adjustment of acenocoumarol dosage using a pharmacogenetic algorithm versus the standard adjustment, in patients initiating oral anticoagulation for the treatment of venous thromboembolism. The follow-up period will be three months (Figure
1). The study will be performed in five separate hospital centers in the Community of Madrid (Spain). The recruitment period started in March 2011 and is scheduled to end in the fourth quarter of 2012.

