### Withdrawal criteria

The patient can discontinue their participation in the study at any time. The research doctor, in his or her opinion or judgment, may also withdraw a patient from the study if required by the patient's clinical situation or if the patient does not comply with the protocol. The onset of chronic disease during the study will result in exclusion of the subject. The continuation of the patient in the study after the onset of acute disease will be at the discretion of the researcher, taking into account the patient's safety and the influence of the disease and/or its treatment on the evaluation variables.

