### Sample size calculation

We need 97 subjects per group to complete the study in order to detect an absolute difference of 20% in the number of patients who are within the therapeutic range on the seventh day after starting the treatment. For this calculation, we have set an alpha error of 0.05 and a beta error of 0.2, and we assume that 40% of the patients will be within the desired INR, and expect this to increase to 60% in the experimental group. Given the risk of drop-out, the number of patients per group will increase by 20%, placing the recruitment objective at 120 patients per group.

According to Caraco *et al*.
[31], pharmacodynamic stabilization with warfarin in the standard control group was achieved in 40.2 ± 21 days. For a reduction in ten days in the experimental group and alpha and beta errors of 0.05 and 0.2 respectively, the required number of patients per group will be 70.

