### Statistical analysis

All recruited patients will be included in the main analysis, following an ‘intention to treat’ (ITT) strategy. For the ITT analysis, patients lost to follow up will be classified in the following way: 1) patients lost before the seventh day will be considered to be outside the therapeutic range; 2) patients lost before the last visit and that have not reached the stable INR will be considered not to be in stable dosing; 3) all lost visits, the INR will be accounted as being out of the therapeutic range. In addition, we will perform a per protocol analysis on all patients who can be monitored for the three month period planned for the study and who have not missed more than one intermediate follow-up visit.

To compare the analysis variables between both groups, a contrast test of the hypothesis will be appropriate based on the normality of the sample (Kolmogorov-Smirnov test), with a Cox regression for dichotomous variables or Kaplan-Meier curves for representing results whenever possible. A regression model (linear or logistic, as appropriate) will be performed when necessary to correct for possible confounding factors. To determine the difference between the two groups in the proportion of time within the therapeutic range, we will use the linear interpolation method proposed by Rosendaal *et al*.
[27]. Finally, we will perform a regression model stratified by center. The value *P* <0.05 will be established as statistically significant, adjusting for multiple comparisons whenever necessary.

The cost-effectiveness analysis will be performed according to a parallel and independent protocol, with special consideration of the direct costs associated with the health care of these patients.

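### The number of special INR measurements is an unscaled count that no loss rule covers, so unequal loss would make the arm that loses more patients look better controlled

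*Protocol article*

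**What the plan says.** All references are to the protocol article.

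- **Definition** (Assessment variables, Secondary): the variable is the "Number of special INR measurements (those that are performed in addition to the scheduled measurements"). Seven INR visits between day 0 and day 90 make up that schedule. The variable has no denominator and no exposure time. The variable listed just above it is scaled to time: "Proportion of time within the therapeutic range, using a linear interpolation method".
- **Duration** (Design and setting): "The follow-up period will be three months".
- **Trigger for extra measurements** (Study procedures, footnote to Table 1): "additional visits can be scheduled as needed, at the discretion of the clinical researcher".
- **Sources of incomplete follow-up**: under Withdrawal criteria the patient may leave at any time, onset of chronic disease leads to exclusion, and the physician "may also withdraw a patient from the study if required by the patient's clinical situation or if the patient does not comply with the protocol". Death is foreseen under Safety. Under Sample size calculation: "Given the risk of drop-out, the number of patients per group will increase by 20" per cent.
- **Main analysis** (Statistical analysis): all recruited patients are included. Loss before day 7 counts as out of range. Loss before the last visit without a stable INR counts as not stable. For "all lost visits, the INR will be accounted as being out of the therapeutic range". A per-protocol analysis of patients followed for three months, with at most one missed intermediate visit, is additional.

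**The concern.** A special INR can be counted only while the patient is under follow-up. An unscaled count therefore falls when follow-up is cut short. The Discussion expects better control to reduce the visits needed, so a low count reads as a good result.

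The plan sets out how losses are scored, and each of its three rules makes loss unfavourable. None applies here. The third deals with scheduled visits that were missed, and a special INR is by definition outside the schedule, so there is no lost visit to score. For this variable alone, loss tends to help the patient's score.

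At stake is the comparison of extra monitoring between arms. If the arms lose patients at different rates or at different times, part of any difference in counts reflects follow-up and not INR control. Unequal loss is possible: the Masking section says the physician is not masked and that this may affect the evaluation variables, and the same physician may withdraw patients. Nothing in the article says which arm would lose more.

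**Working it through.** **The plan's own figures.** The article gives no expected number of special INRs, so there is no stated figure to reproduce for this variable. For the setting I use its 120 per group. Adding 20% to 97 gives 97 × 1.2 = 116.4, and dividing by 0.8 gives 121.25, so 120 lies between the two conventions. It allows a loss of (120 − 97)/120 = 19.2%.

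**Assumptions (not in the article).** Three special INRs per full 90 days in both arms, with no true difference; patient rates gamma-distributed with shape 2 (gamma-Poisson counts); loss unrelated to a patient's own rate; loss times uniform either over days 0–90 (even) or over days 0–30 (early). Loss splits are 20% v 20%, 15% v 25% and 10% v 30%.

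**Step 1: how a lost patient scores, constant rate.** The mean count is 3 × (mean time observed / 90).

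- Completer: mean 3.0; probability of zero (1 + 3/2)^−2 = 16%.
- Early loss: mean 3 × 15/90 = 0.5; probability of zero, averaged over the loss time, 2 − 2/1.5 = 67%.
- Even loss: mean 3 × 45/90 = 1.5; probability of zero (2 − 2/2.5)/3 = 40%.

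**Step 2: arm means, constant rate.** With loss proportion d, the fraction of the full count that is observed is 1 − d × 0.5 (even) or 1 − d × (1 − 15/90) = 1 − d × 0.833 (early).

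| Loss | Even | Early |
|---|---|---|
| 20% v 20% | 0.900 v 0.900, ratio 1 | 0.833 v 0.833, ratio 1 |
| 15% v 25% | 0.925 v 0.875, 5.4% lower | 0.875 v 0.792, 9.5% lower |
| 10% v 30% | 0.950 v 0.850, 10.5% lower | 0.917 v 0.750, 18.2% lower |

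**Step 3: arm means if special INRs cluster early.** Assume an intensity that decays exponentially with a 20-day constant. The fraction accrued by day t is (1 − e^(−t/20))/(1 − e^(−4.5)). Averaged over the loss time, a lost patient has accrued 0.789 of the full count (even; about 2.4 of 3) or 0.487 (early; about 1.5 of 3).

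- 15% v 25%: 0.947/0.968, 2% lower (even); 0.872/0.923, 6% lower (early).
- 10% v 30%: 0.937/0.979, 4% lower (even); 0.846/0.949, 11% lower (early).

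**Step 4: false-positive rates.** I simulated 3,000 trials per scenario, 120 per arm, equal true rates, two-sided 5% level. The columns are a t-test on raw counts; a Poisson rate ratio with one log-follow-up offset and robust standard errors; and the same model with follow-up split at days 3, 7, 15, 30 and 60, period as a factor, clustered by patient. Center was not simulated.

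| Rate over time, 10% v 30% loss | Raw count | Single offset | Split by period |
|---|---|---|---|
| Constant, even / early | 13% / 32% | 6% / 5% | 6% / 5% |
| 20-day decay, even / early | 6% / 14% | 8% / 11% | 5% / 5% |
| 10-day decay, even / early | 5% / 9% | 12% / 19% | 6% / 6% |

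At 15% v 25% with a constant rate, the raw count gives 8% (even) and 12% (early). At 20% v 20% it gives 5–6% throughout. The split model gave 4–6% in all 18 scenarios. Under early clustering at 10% v 30%, the single offset gives an average rate ratio of 1.07 to 1.14 when the truth is 1, so the arm that loses more then looks worse.

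**The case against.** **A full analysis plan may deal with this.** The article is condensed. It names no test for this variable and does not say that raw counts will be compared regardless of follow-up. This limits the weight of the point. It does not remove it: the article itself defines the variable as a number, fixes the analysis set, and states its loss rules without covering this variable.

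**The per-protocol analysis equalises follow-up.** It nearly does, and it would help to reveal a gross artefact. But it is additional and selects on completion after randomization, so it is only a partial check.

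**Bias between arms needs unequal loss.** Correct. A reader might infer that the comparison is biased at the planned 20% drop-out. It is not, if loss has the same size and timing in both arms. No passage suggests 10% v 30%, and the article plans the same allowance for each group.

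**A lost patient does not always get the best score.** Also correct. Zero is likely only for very early leavers; someone withdrawn after an unstable start may already have several special INRs.

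**An offset can do harm.** This stands for a single offset over the whole follow-up. Under early clustering it had the higher false-positive rate in three of the four 10% v 30% scenarios. It does not stand for a model split by period.

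**Link to efficiency.** A reader might tie this variable to the efficiency objective. The article assigns that objective to a separate economic protocol and does not connect the two.

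**Conclusion.** The point holds in a limited form. As defined, the count rewards short follow-up, and the plan's loss rules, which penalise loss for the in-range and stable-INR variables, do not reach it. Equal loss only lowers both means. With unequal loss and a constant rate, the arm that loses more looks about 5% to 10% better at 15% v 25%, and about 10% to 18% better at 10% v 30%. With a 20-day decay these ranges fall to 2–6% and 4–11%.

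The sizes rest on assumed loss splits, loss timing and time course of special INRs. The false-positive rates also depend on the assumed mean and dispersion. A headline error rate of 30% or more would need a threefold imbalance in loss, concentrated in the first month, together with a constant rate; the article supports none of these. No primary variable and no sample-size figure depends on this count, so it is a minor point.

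**What to change.** Under Assessment variables and Statistical analysis, state that special INRs are counted from day 0 to day 90 only while the patient is under follow-up. Then choose one of two comparisons:

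1. A rate ratio from a negative binomial or robust Poisson model, with log time at risk as offset, follow-up split at the scheduled visits (period as a factor, clustered by patient) and center as a factor.
2. The mean cumulative number of special INRs to day 90, censored at last contact, with death handled as a terminal event.

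Do not use a single offset over the whole follow-up. Report raw counts, deaths and losses by arm beside the result. Either method still assumes that, within an arm, leaving early is unrelated to the need for special INRs, so the reasons for loss should be shown.

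The cost is a change of wording and slightly more analysis work, with a rate ratio (option 1) or a difference in mean cumulative counts (option 2) in place of a simple difference in counts. Study procedures already sends all INR measurements to the CRF. The article does not say that the date of last contact is recorded there, so that should be confirmed. The sample size does not change.
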